### Hypotheses

In the first step, we will examine the trainability of the avoidance of snacks. Thereby, we assume that the children in the intervention group show lower contingent reaction times (pull the vegetable and push the snacks away) in comparison to the control group (see [26]). Since we postulate that the improvement of the children’s ability to self-regulate is an essential determinant for their sustained weight loss, the efficacy of our newly developed computer training program has to be tested in the first step. Evidence of the training effect is the basis for the testing of the further hypotheses.

The primary hypothesis postulates that children in the intervention group will experience a more sustained reduction of their BMI-SDS at the 6- and 12-month follow-up than children in the control group. Secondary hypotheses postulate that children in the intervention group - compared to the placebo control group - will experience a more pronounced and sustained improvement in their self-regulation skill. We further expect a more pronounced and sustained increase in the quality of life among the intervention group as well as a healthier eating behavior (in terms of lower snack consumption). In an exploratory manner, we will explore whether children with a more pronounced binge eating behavior (indicating more self-regulation problems) will profit more from the approach-avoidance training. In contrast, however, we expect children with more pronounced psychosocial strain (internalizing and/or externalizing behaviour problems) will profit less from our intervention than children exhibiting no psychosocial problems.

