### Measures

In the SRT-Joy, the AAT registers the reaction times of the children as they use approach-pull movements and avoid-push movements toward the images shown on the screen. In a pilot study, we could already provide evidence that children showed improved reaction times after six training sessions. In line with the other studies [26], we will calculate different indicators: reaction times for snacks (compatible and incompatible reactions), reaction times for vegetables and a so-called compatibility index (reaction times (compatible tasks) – reaction times (incompatible tasks) [26]). The compliance with the treatment protocol can be directly assessed via log-in times of the children. The acceptance of the computerized treatment approach will be assessed via a self-constructed questionnaire at the end of the training. At the beginning and end of each session, the degree of hunger, appetite, and the current mood will be assessed as possible confounding factors.

The Implicit Association Test (IAT) is used to capture the attitude toward snacks. The task is to assign a positive or a negative category to the images and words presented on the screen. The IAT [32] is based on the assumption that when there is a positive association between the positive category (here: “good”) and the target object (here: snacks), the reaction time is shorter (in this example: category “good” and snack image), whereas in a pairing of the negative category (“bad”) and the target object (snacks), the reaction is assumed to be slower because an implicit positive “bias” exists toward snacks.

As a behavioral indicator for the child’s inhibition capacity, a Stroop test is used. Color words are presented on the screen either in congruent (the word “red” typed in red-colored letters) or incongruent (the word “red” typed in blue) writing colors. Children under the age of 12 will be asked to fill in a paper-pencil Fruit Stroop test (images of fruits in different colors; [33]), which works on the same principles as the Stroop test conducted on the computer. The color either corresponds to the actual color of the fruits or not (example congruent: yellow banana, incongruent example: blue banana). There is evidence that the Stroop Test paradigm is a reliable and valid paradigm for assessing the inhibitory control of children (for example, [34]).

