### Data analyses

Missing data of the computer-assisted measurements will not be replaced since there are very unlikely and might be a sign of recording problems. With respect to the questionnaire data and the primary outcome, missing values will be replaced by unbiased substitution (EM-algorithm). As a first step, an analysis of whether the children in the intervention group show a learning effect compared to the control will be conducted. This learning effect would be characterized by faster reaction times at the end of the training. Primary and secondary outcomes will be tested performing an ANCOVA from post-intervention to the 12-month follow-up between the two random groups, adjusted for the baseline measurements. They will be analyzed by performing an ITT as well as a per-protocol analysis (PPA) that excludes all drop-outs. The association between self-regulation and sustained weight loss at 12-month follow-up and potential moderators (binge eating; psychosocial strain) will be tested using hierarchical multiple regression analyses. As a second step, the BMI-SDS change will be dichotomized (successful versus not successful) in order to perform logistic regression analyses. Relevant trial results will be published in the corresponding platforms.

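### The Hypotheses section reads as making the BMI-SDS test depend on a reaction-time training effect, while Data analyses states that test without a condition; the two must be reconciled

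*Protocol article*

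**What the plan says.** The Hypotheses section begins with the trainability of snack avoidance. It argues that better self-regulation is a key determinant of lasting weight loss and that for this reason "the efficacy of our newly developed computer training program has to be tested in the first step". It then adds: "Evidence of the training effect is the basis for the testing of the further hypotheses". The next paragraph opens with the weight hypothesis: "The primary hypothesis postulates that children in the intervention group will experience a more sustained reduction of their BMI-SDS", at 6 and 12 months.

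The Data analyses section keeps the order: "As a first step, an analysis of whether the children in the intervention group show a learning effect" relative to control. It then moves to the main analysis: "Primary and secondary outcomes will be tested performing an ANCOVA from post-intervention to the 12-month follow-up", with intention-to-treat and per-protocol versions. That sentence neither repeats the condition nor says that the primary test goes ahead if the first step shows nothing.

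The Primary and secondary outcomes section names BMI-SDS course as the one primary outcome. The Sample size and enrolment section bases 199 children on a single ANCOVA with f = .2, power .8, alpha .05 and three covariates. It plans 226 allocated, with intention-to-treat analysis on all 226.

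**The concern.** Read literally, the Hypotheses section sets a sequence: show a reaction-time effect, then test weight. If the first step failed, the randomised weight comparison, for which 226 children are followed for a year, would either not be formally tested or be tested against the protocol's own rule.

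The sequence protects nothing in return. With one primary outcome, the BMI-SDS test holds its 5% level without a preceding test. A null training effect would change how a weight difference is explained, but it would not make the randomised comparison invalid.

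A precondition can only lower the chance that the primary hypothesis is both reached and found significant. The planned power therefore describes a test without the gate.

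**Working it through.** **1. The text.** The Hypotheses section states a precondition. Data analyses states an order and then an unconditional ANCOVA. No section gives a significance level for the first step, a criterion for passing it or a consequence of failing it, and none lifts the precondition. A reader cannot tell which rule applies after a null first step.

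**2. The plan's own figure.** Inputs from Sample size and enrolment: f = .2, alpha .05, power .8, two groups, three covariates. For the ANCOVA F test with 1 and N − 2 − 3 degrees of freedom and noncentrality λ = f² × N:

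- N = 198: power .7996
- N = 199: λ = .04 × 199 = 7.96, power .8016

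The smallest N reaching .80 is 199, as stated. The figure is reproduced for a primary test with no gate. At N = 226, λ = .04 × 226 = 9.04 and power is .849. (The protocol's .9 at 226 comes from a compromise analysis whose error ratio is not given, so it is not used here.)

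**3. Power through the gate.** Assumptions, none of them in the protocol: the gate is passed at alpha .05, it is tested with the same type of ANCOVA at the same N, and its effect size is f = .15 to .40. The protocol expects average-sized effects for the self-control measures but gives no number; f = .25, the usual medium value, is taken as the nearest reading.

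With independent tests, P(both significant) = gate power × primary power. For example, at f = .25:

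- N = 199: .939 × .802 = .753
- N = 226: .963 × .849 = .818

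For correlated test statistics, the joint probability is Φ₂(z_gate, z_primary; ρ), where each z is the normal quantile of that test's power.

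| Gate effect (assumed) | N | Gate power | Primary power, no gate | Power through gate, ρ = 0 to .5 |
|---|---|---|---|---|
| f = .40 | 199 | 1.000 | .802 | .802 to .802 |
| f = .40 | 226 | 1.000 | .849 | .849 to .849 |
| f = .25 | 199 | .939 | .802 | .753 to .775 |
| f = .25 | 226 | .963 | .849 | .818 to .832 |
| f = .20 | 199 | .802 | .802 | .643 to .689 |
| f = .20 | 226 | .849 | .849 | .721 to .757 |
| f = .15 | 199 | .558 | .802 | .447 to .505 |
| f = .15 | 226 | .612 | .849 | .520 to .568 |

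At f = .25 the loss is .802 − .753 = .049 down to .802 − .775 = .027 at N = 199, and .849 − .818 = .031 down to .849 − .832 = .017 at N = 226. The chance that the primary hypothesis is never formally reached is 1 − .939 = 6% and 1 − .963 = 4%.

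**The case against.** The strongest reply is that no gate was intended. The sentence follows a theoretical argument and may describe only causal logic or the order of analysis. The analysis section, where a testing rule would be expected, states the ANCOVA without a condition, and the sample size section commits to intention-to-treat analysis of all 226. This stands as far as it goes: a reader might infer that the primary outcome will definitely go untested if the first step fails, and the documents do not establish that. But they do not exclude it either, and the Hypotheses wording is stronger than a statement of order.

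Three further criticisms are tempting but not supported:

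- **The gate measures mere practice.** The phrase "This learning effect would be characterized by faster reaction times at the end of the training" and the pilot remark that "children showed improved reaction times after six training sessions" could suggest that raw speed decides. But Hypotheses refers to contingent reactions compared with control, and Data analyses also compares with control. The placebo arm has the same number and structure of sessions. General practice gains occur in both arms, and randomisation balances age in expectation. The pilot remark does not define the gate. Which reaction-time indicator is used can be left to the analysis plan.
- **The gate rests on different children.** The rule that "Missing data of the computer-assisted measurements will not be replaced" is followed by the reason that such gaps are very unlikely, and the training data are collected during the inpatient stay. A material difference from the intention-to-treat set is speculation.
- **Power collapses to .64 or .45.** Those values need gate effects of f = .20 and .15 with independent tests. Both effects lie below the protocol's expectation for skills that the training targets directly, and independence sits badly with the trial's premise that self-regulation drives weight loss.

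**Conclusion.** The concern holds as an unreconciled conflict between Hypotheses and Data analyses. On its plain reading, the former could leave the sole primary outcome formally untested. The precondition brings no type I error benefit and is absent from the sample size.

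The direction of the power effect is certain if the gate is applied; its size is not. With an assumed medium training effect, the loss is about 3 to 5 percentage points at N = 199 and 2 to 3 at N = 226, where power stays above .80. It is close to nil for a large effect and becomes serious only at f = .20 or below. The case for changing the text therefore rests mainly on keeping the main question unconditional, and only secondarily on power.

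**What to change.** Replace the conditional sentence in Hypotheses with: *The BMI-SDS primary hypothesis is tested in all randomised children regardless of the training-effect result.* Repeat this in Data analyses next to the ANCOVA, so that the two sections agree. Keep the between-arm training effect as the first reported analysis, labelled as a manipulation check that aids interpretation of the weight result.

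This changes wording only. It needs no extra children or data and has no type I error cost, because the single primary outcome is still tested once at its stated level. It also makes the published calculation of 199 apply to the test that will actually be done.

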### Measures

In the SRT-Joy, the AAT registers the reaction times of the children as they use approach-pull movements and avoid-push movements toward the images shown on the screen. In a pilot study, we could already provide evidence that children showed improved reaction times after six training sessions. In line with the other studies [26], we will calculate different indicators: reaction times for snacks (compatible and incompatible reactions), reaction times for vegetables and a so-called compatibility index (reaction times (compatible tasks) – reaction times (incompatible tasks) [26]). The compliance with the treatment protocol can be directly assessed via log-in times of the children. The acceptance of the computerized treatment approach will be assessed via a self-constructed questionnaire at the end of the training. At the beginning and end of each session, the degree of hunger, appetite, and the current mood will be assessed as possible confounding factors.

The Implicit Association Test (IAT) is used to capture the attitude toward snacks. The task is to assign a positive or a negative category to the images and words presented on the screen. The IAT [32] is based on the assumption that when there is a positive association between the positive category (here: “good”) and the target object (here: snacks), the reaction time is shorter (in this example: category “good” and snack image), whereas in a pairing of the negative category (“bad”) and the target object (snacks), the reaction is assumed to be slower because an implicit positive “bias” exists toward snacks.

As a behavioral indicator for the child’s inhibition capacity, a Stroop test is used. Color words are presented on the screen either in congruent (the word “red” typed in red-colored letters) or incongruent (the word “red” typed in blue) writing colors. Children under the age of 12 will be asked to fill in a paper-pencil Fruit Stroop test (images of fruits in different colors; [33]), which works on the same principles as the Stroop test conducted on the computer. The color either corresponds to the actual color of the fruits or not (example congruent: yellow banana, incongruent example: blue banana). There is evidence that the Stroop Test paradigm is a reliable and valid paradigm for assessing the inhibitory control of children (for example, [34]).

The dot probe task is a measure of selective attention. During this computer task, two stimuli (for example, words or images) are simultaneously presented on the screen. One stimulus corresponds to a particular target concept (food), and the other stimulus is neutral. Subsequently, one of the two stimuli is replaced by a dot. The participant is instructed to respond as quickly as possible to the position of the dot by a specific keystroke. Children with a selective attention to food stimuli are expected to react more quickly when the dot replaces the food stimulus compared to the neutral stimulus (for example, [35]).

These computerized mainly food-related behavioural tests will be conducted at the beginning (T1) and end (T2) of the inpatient stay. On the basis of these data, whether the SRT-Joy Training leads to an immediate improvement of the self-regulation abilities of the overweight children (training effect) will be analyzed.

### Primary and secondary outcomes

The primary outcome of the study is the BMI-SDS course, that is, the sustained weight loss after the intensive inpatient lifestyle intervention. Weight and height data of the children will be measured at the beginning and the end of their rehabilitation stay by means of a standard beam scale (accurate to 100 g) and a calibrated stadiometer (accurate to 1 cm). In order to account for sex and age differences, a BMI-SDS will be calculated [29]. In order to receive unbiased anthropometric data at the follow-ups as well, the children will be asked to visit their family physician, who will be blind to trial-group assignment and the study goals. The families (and their physicians) will be reminded several times (by mail and telephone) and reimbursed for their efforts in order to decrease attrition bias.

The secondary outcome is the child’s ability to self-regulate. Self-regulation encompasses conscious as well automatic efforts to achieve long-term goals [9]. In order to assess conscious aspects of self-regulation skills, the Brief Self-Control Scale (BSCS) will be administered. The BSCS by Tangney, Baumeister, and Boone [36] was translated into German and adapted for children, using a multistage process. The 13 items (for example, “I am good at resisting temptations”) will be rated on a five-point Likert scale from “strongly disagree” to “agree.” Higher values indicate a more pronounced self-control. In addition, the parents will also judge the self-control skills of their children as a proxy-report. Furthermore, the self-efficacy experience of the children will be assessed using an adaptation of the weight-specific self-efficacy questionnaire for children and adolescents [37]. The nine items cover the child’s confidence to deal with current temptations of sweets (for example, “How sure are you … to refrain from sweets, although they taste good?”) on a five-point scale ranging from “highly uncertain” to “very confident.” Since both methods have been adapted for the study, the psychometric properties will be assessed in a parallel sample.

In addition to these measures, we will assess weight-related quality of life and the food intake of the children. Using the weight-specific quality of life questionnaire for overweight and obese children and adolescents (GW-LQ-KJ) the weight-related quality of life will be measured. The 11 items (for example, “During the last two weeks I felt blue because of my weight”), rated on a 5-point Likert scale, reach high internal consistencies (α = 0.87) [37, 38]. Children’s food intake will be evaluated using a short nine-item food frequency list including “healthy” (vegetables and fruits) and “problematic” food items (for example, sugared drinks, salty snacks, and sweets). Children are asked to rate their usual intake on a five-point scale (“never” to “several times a day”). In a previous study (Warschburger P et al.: Empowering parents of obese children (EPOC): A randomized-controlled trial on additional long-term weight effects of a parent training, submitted) , reliability was acceptable for the “healthy food intake” scale (α = .78) but low for the “problematic scale” (α = .53). In order to increase the reliability of the latter scale, it was expanded with additional items (for example, eating fast food and sweet dairy products) for the present study.

### Predictors

Binge eating will be assessed via a child’s self-report on experiencing attacks of binge eating and psychosocial strain with the parent version of the Strengths and Difficulties Questionnaire (SDQ), a reliable and valid screening questionnaire [39].

### Randomization procedure and treatment allocation

Randomization and allocation in a ratio of 1:1 for each clinic to treatment aim will occur before the interventions begin. The randomization is computer based [40] and centrally performed. A post-hoc evaluation by descriptive statistical comparisons between the intervention and the control group in relevant sociodemographic data (age, gender, and sociodemographic data) will be conducted to assess the effectiveness of the randomized assignment. The study assistant will receive the fax with the randomization that only discloses the allocation of the patients to either group A or B (allocation concealment).

### Points of measurement

The data are collected by questionnaires and computer assessment for children at four points of measurement. Assessment of the pre-intervention (T1) and post-intervention (T2) data will be conducted at the clinic during the inpatient stay, the follow-up measurements for the 6- and 12-month follow-up at home. At the beginning (T1) and the end (T2) of the inpatient stay, the weight status (the primary outcome) is assessed by the physician in charge. Children and their parents fill in the self- and proxy-report questionnaires, respectively. The computer-assisted assessment (AAT; IAT; dot probe and Stroop) will be conducted directly before and after the last training session. Two follow-up assessments will take place, the first, 6 (T3) and the second 12 (T4) months after the [41] discharge from the clinic and at the end of the intervention. Questionnaires will be sent via mail in order to collect the self-report and proxy-report data. In addition, objective weight and height measurements will be conducted by the physician of the participant using calibrated measurement devices. In order to receive the weight-related data of the follow-up measurements, the patients are asked to grant the study center permission to contact their physician in order to achieve the relevant data. Additional information for the follow-up assessments will also be collected with the use of questionnaires respective computer tests. The follow-up assessment will also include questions regarding the utilization of additional weight-loss interventions, as this might influence the primary endpoint.

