## Methods/Design

### Study design

The Self-Regulation Training Joystick (SRT-Joy) is a multicenter, prospective, parallel group, randomized-controlled superiority trial for the evaluation of the efficacy of a computer-assisted individual self-regulation training compared to a placebo control group. Depending on their intervention allocation, children play either the SRT-Joy computer task or the placebo training. In order to obtain information on the transfer of increased self-regulation skills to everyday life, two follow-up measurements after the end of the inpatient rehabilitation stay will be realized. Hence, the four time points for measurement are given below: start of the child’s inpatient stay and beginning of the computer training (T1), end of the child’s computer training during the inpatient stay (T2), 6 months after the child’s inpatient stay (T3), and 12 months after the child’s inpatient stay (T4). The trial flow is depicted in Fig. 1.

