### Intervention and controls

#### Basic interventions for all children

The inpatient stay usually encompasses a period of 4 weeks. During their stay, all children and adolescents will participate in a multidisciplinary lifestyle intervention, which includes cognitive-behavioral group training, nutrition education, and diet modification, as well as activity sessions several times a week. This complex treatment approach focuses on the increase in physical activity, the decrease in sedentary behavior, the change in eating habits, and the relative reduction of weight. The AAT treatment will be implemented as a supplemental treatment offer of the clinics.

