#### SRT-Joy Approach-Avoidance-Training: intervention

Children and adolescents far too often eat high-caloric snacks and too seldom vegetables [31]. Therefore, they should learn, in the context of the computer-based training, to push high calorie snacks away and to pull vegetables with the joystick toward themselves. In a pilot study, these foods have been tested on their familiarity and have been matched according to their color. All foods are presented on white either square or round plates. Children are instructed to use the approach response with the round plate (pull) and the avoidance response (push) with the square one using the joystick. Thereby, the vegetables are always located on the round plates and the snacks on the square plates (implicit approach-avoidance training). Contingent with their actions, the photos on the screen get either larger or smaller. A short instruction phase ensures that the children have understood the instructions. This phase is followed by a test trial (pre-test data) and the training phase (including six training blocks). In each training session, the children will view 120 pictures. Compatible (vegetables on round plates, snacks on square plates) and incompatible stimuli are balanced per trial. The training phase is followed by an assessment of the post-data and a booster training. At the end of each training session, the children receive a feedback on their error rate and their reaction time. The training sessions take approximately 15 to 30 min each and are conducted during 3 consecutive days followed by a pause of 4 days over the course of the first 2 weeks of rehabilitation (six appointments).

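### The computer-assisted tests have two incompatible schedules, and T2 means the end of training in some sections and the end of the stay in others

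*Protocol article*

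**What the plan says.** Five places in the protocol article bear on when the computer-assisted tests are done and what T2 means.

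- Points of measurement, on the tests: "The computer-assisted assessment (AAT; IAT; dot probe and Stroop) will be conducted directly before and after the last training session".
- Measures, on the same tests: "These computerized mainly food-related behavioural tests will be conducted at the beginning (T1) and end (T2) of the inpatient stay". Their stated purpose follows: "whether the SRT-Joy Training leads to an immediate improvement of the self-regulation abilities of the overweight children (training effect) will be analyzed".
- Study design places T1 at the start of both the stay and the training, and T2 at the end of the child's "computer training during the inpatient stay (T2"). The Abstract likewise ties the post assessment to the end of training.
- Points of measurement, on weight: "At the beginning (T1) and the end (T2) of the inpatient stay, the weight status (the primary outcome) is assessed". Primary and secondary outcomes also has children weighed at the start and end of the stay.
- The calendar comes from the two intervention sections. Training runs "over the course of the first 2 weeks of rehabilitation (six appointments"), and "The inpatient stay usually encompasses a period of 4 weeks".

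Randomization procedure and treatment allocation has allocation done before the interventions start. Blinding has the pre-assessment done before randomization.

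**The concern.** A pre-post contrast has a meaning only if both dates are fixed. Here the pre-test date is stated in two incompatible ways, and so is the post-test date.

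If the sentence under Points of measurement is followed as written, the pre-test is not a baseline, because most of the training has already been delivered. If only the post-test is in question, it falls either right after the last session or at discharge about two weeks later. The first measures what training does at once. The second measures what is left after a further period of inpatient treatment without training. The Measures section asks for the immediate effect but schedules the tests at the end of the stay.

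The double meaning of T2 carries the problem further. Data analyses starts the ANCOVA of primary and secondary outcomes at post-intervention, and a reader cannot tell from the label alone which of the two dates that is.

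**Working it through.** The plan gives no figure of its own to reproduce here. The check sets the sections side by side and then does day arithmetic.

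**Side by side**

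| Section | Pre-test or T1 | Post-test or T2 |
|---|---|---|
| Abstract | start of rehabilitation | end of training |
| Study design | start of stay and of training | end of training |
| Measures (computer tests) | start of stay | end of stay |
| Points of measurement (computer tests) | just before the last session, if read literally | just after the last session |
| Points of measurement (weight) | start of stay | end of stay |
| Primary and secondary outcomes (weight) | start of stay | end of stay |
| Blinding, with Randomization | before allocation, hence before training | not stated |

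**Pre-test.** Inputs: six sessions of 120 pictures each (SRT-Joy intervention section).
- Sessions completed before a test placed directly ahead of the sixth: 6 − 1 = 5, and 5/6 = 83 %.
- Pictures already seen: 5 × 120 = 600 of 6 × 120 = 720.

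The literal pre-test would therefore come after 83 % of the training. The Measures, Study design, Randomization and Blinding sections all rule this out.

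**Post-test and T2.** Inputs: three consecutive days, a four-day pause, three further days, all within the first 2 weeks; a stay of usually 4 weeks, taken as 28 days.
- First session on day s gives sessions on days s, s+1, s+2, s+7, s+8 and s+9.
- The last session must fall by day 14, so s + 9 ≤ 14 and s lies between 1 and 5.
- s = 1: last session on day 10, gap to day 28 = 18 days.
- s = 5: last session on day 14, gap to day 28 = 14 days.

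The two meanings of T2 are thus 14 to 18 days apart, at least half of the stay.

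**Weight.** Both sections that describe the weighing give the end of the stay. The only conflict is with the T2 or post label in the Abstract and in Study design.

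**The case against.** The strongest reply is that the sentence under Points of measurement is a slip for a test before the training starts and another after the last session. This is plausible. The same section opens by speaking of pre-intervention and post-intervention data, and four other sections fit that reading. It removes the pre-test conflict but not the post-test one: a test after the last session falls in about week 2, and Measures still puts it at the end of the stay.

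The article also says that study coworkers are trained and given a manual (Trainer meetings and monitoring). The manual is not shown and may settle practice at the centres. The published text would still be contradictory.

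A reader might infer more than the document supports:

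- **That the evidence on which the later hypotheses depend is lost.** Hypotheses makes the reaction-time effect in the AAT the basis for later testing. The SRT-Joy section describes a test trial before the training phase and a further assessment after it. If this describes every session, which is the natural reading, AAT pre-test data exist from session 1. The IAT, dot probe and Stroop have no such second source, but later testing is not made conditional on them.
- **That the T2 weight is taken in week 2.** No section schedules a weighing then.
- **That power for the training effect collapses.** The article gives no numerical effect size for the self-control measures, only an expectation of average effects. Any power figure would also rest on the least plausible reading of the pre-test sentence.
- **That the group comparison is biased.** Both arms have the same number and structure of sessions, and allocation is 1:1 within each clinic, so a shared timing ambiguity does not by itself favour either arm.

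**Conclusion.** The contradiction is in the current text and should be corrected. It is not a matter of detail left to a fuller document, because the article states incompatible timings. The literal pre-test falls after five of six sessions, and the two meanings of T2 differ by about 14 to 18 days. That range assumes a 28-day stay and the stated pattern of training days; since the stay is only usually 4 weeks, it is approximate.

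What remains open is whether the computer tests show an immediate training effect or retention at discharge, and which date the label T2 denotes. If centres followed different sections, their test data would not be comparable; nothing in the article shows that this has happened. The timing of the primary outcome is not in doubt. This is a drafting inconsistency that affects the process measures and the T2 label.

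**What to change.** - Reword Points of measurement so that the computer-assisted pre-test comes before the first training session (T1).
- Fix one post-test time for these tests. If the immediate training effect is the target, as Measures says, this is after the last session. If a test at discharge is also wanted, name it as retention.
- Give the end-of-training assessment and the discharge assessment of weight separate labels. Use them consistently in the Abstract, Study design, Measures, Points of measurement and Data analyses, and state which one post-intervention means for each outcome.
- Send the clarification to all four centres, and record the actual date of each computer test, including those already done.

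The article reports recruitment as ongoing, so this can still help. The cost is a protocol clarification and a site memo. Settling on one pre-test and one post-test adds no visits.
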